# LIST OF ABBREVIATIONS AND RELEVANT DEFINITIONS

| ABR | ABR form, General Assessment and Registration form, is the application form that is required for submission to the accredited Ethics Committee (In Dutch, ABR = Algemene Beoordeling en Registratie) |
| --- | --- |
| AE | Adverse Event |
| AVG | General Data Protection Regulation (in Dutch Algemene Verordering Persoonsgegevens) |
| AHSP | Appetite, Hunger and Sensory Perception |
| AR | Adverse Reaction |
| CCMO | Central Committee on Research Involving Human Subjects; in Dutch: Centrale Commissie Mensgebonden Onderzoek |
| CTN | Chorda tympani nerve |
| CV | Curriculum Vitae |
| DSMB | Data Safety Monitoring Board |
| eCRF | electronic Case Report Form |
| EGM | Electrogustometer |
| GCP | Good Clinical Practice |
| IB | Investigator’s Brochure |
| IC | Informed Consent |
| METC | Medical research ethics committee (MREC); in Dutch: medisch ethische toetsing commissie (METC) |
| MTPRT | Macronutrient and Taste Preference Ranking Task |
| (S)AE | (Serious) Adverse Event |
| SPC | Summary of Product Characteristics (in Dutch: officiële productinfomatie IB1-tekst) |
| Sponsor | The sponsor is the party that commissions the organisation or performance of the research, for example a pharmaceutical  company, academic hospital, scientific organisation or investigator. A party that provides funding for a study but does not commission it is not regarded as the sponsor, but referred to as a subsidising party. |
| SUSAR | Suspected Unexpected Serious Adverse Reaction |
| TST | Taste Strip Test |
| WMO | Medical Research Involving Human Subjects Act (in Dutch: Wet Medisch-wetenschappelijk Onderzoek met Mensen) |

**SUMMARY**

**Rationale:** The chorda tympani nerve (CTN) is a mixed nerve, which carries sensory and parasympathetic fibers. The sensory component supplies the taste sensation of the anterior two-thirds of the ipsilateral side of the tongue. During middle ear surgery the CTN is exposed and frequently stretched or sacrificed, because it lacks a bony covering as it passes the middle ear. The injury may cause hypogeusia, ageusia or altered taste sensation of the ipsilateral side of the tongue. Patients may also suffer from a dry mouth. To date, there is no consensus regarding which type of CTN injury, obtained during primary stapes surgery and primary cochlear implantation, gives the least burden.

**Objective:** To determine whether damaging the CTN during primary stapes surgery and primary cochlear implantation influences postoperative taste function and to determine which type of injury is associated with worse postoperative taste function. Taste function will be measured using taste strips.

**Study design:** A prospective study.

**Study population:** Adult patients, 18 years and older, who are eligible for primary stapes surgery or primary cochlear implantation

**Main study parameter:** Amount of identified taste strips of the ipsilateral tongue to the operated ear (range 0 – 20).

**Nature and extent of the burden and risks associated with participation, benefit and group relatedness:** Patients will not experience any risks during participation in the study. There will be four test sessions. Each time, all participants complete two taste tests and a macronutrient an taste preference ranking task and fill out several sets of questionnaires. The test sessions will take place in the University Medical Center Utrecht during the regular visits of the patient to the hospital. Three months after surgery the taste sensation is evaluated at home using questionnaires. The study burn is moderate. We believe that the burden is in proportion to the potential value of the research.

# 1. INTRODUCTION AND RATIONALE

The chorda tympani nerve (CTN), a branch of the facial nerve, is a mixed nerve, which carries sensory and parasympathetic fibers. The sensory component supplies the taste sensation of the anterior two-thirds of the ipsilateral side of the tongue. The parasympathetic component innervates the submandibular and sublingual salivary gland. The CTN passes the medial surface of the neck of the malleus and runs in between the malleus and the incus in the tympanic cavity. The CTN leaves the tympanic cavity together with the anterior tympanic artery through the anterior canaliculus. The nerve continues through the petrotympanic fissure and runs towards the infratemporal fossa. This is where the CTN merges with the lingual nerve. During middle ear surgery, the CTN is exposed and frequently stretched or sacrificed, because it lacks a bony covering as it passes the middle ear. The injury may cause hypogeusia, ageusia or altered taste sensation of the ipsilateral side of the tongue. Patients may also suffer from a dry mouth (1).

To date, there is no consensus regarding which type of CTN injury, obtained during primary stapes surgery or primary cochlear implantation, gives the least burden. Some articles concluded that the taste outcome is better if the CTN is sacrificed instead of the CTN being preserved but damaged by stretching (2–5). Other articles report that sacrificing the CTN results in more taste disturbance compared to nerve preservation (6–9). Lastly, Rice et al. concluded that sacrificing or preserving the CTN makes little difference for the patient. Sparing the CTN may hinder an adequate view of the middle ear structures during surgery. If in fact sacrificing the CTN leads to less or equal taste disturbance compared to stretching it, sparing the CTN would not be justified (10).

A recently published systematic review of the effect of CTN injury during noninflammatory middle ear surgery concluded that patients with a stretched CTN were slightly more symptomatic than patients with a sacrificed CTN. The included studies were characterized by several limitations in their study design. The follow-up duration varied greatly between the included studies with a range of 6 weeks to 99 months. A longer follow-up duration may result in fewer symptoms due to the longer recovery time or habituation of symptoms (1). Secondly, age seems to be associated with recovery rate. Younger patients seem to have significantly higher recovery rates of CTN function compared to older patients (11). Most of the included studies disregarded age. Thirdly, postoperative taste dysfunction may have been underreported. It is not clear whether surgeon routinely asked their patients about taste dysfunction in the included studies. Lastly, most studies did not include quality of life as an outcome measure and therefore it remains unclear whether taste dysfunction significantly impacts quality of life (1).

*Purpose of this study*

A lack of high quality studies on the subject precludes firm evidence-based recommendations and demonstrates the need for a high-quality study. In order to accommodate this need, in the proposed double-blind prospective study we will investigate the effect of CTN injury on postoperative taste disturbance and quality of life.

# 2. OBJECTIVES

Primary Objective:

To evaluate the effect of CTN injury on postoperative taste function measured using taste strips in patients undergoing primary stapes surgery or primary cochlear implantation.

Secondary Objective(s):

- To compare the postoperative taste function of sweet, sour, bitter, salty and umami measured using taste strips in patients between two types of CTN injury (stretching or sacrificing)
- To compare the postoperative EGM threshold in uA for different locations of the tongue in patients between two types of CTN injury (stretching or sacrificing)
- To compare the presence of postoperative symptoms of taste disturbance in patients between two types of CTN injury (stretching or sacrificing).
- To compare the postoperative perception of appetite, hunger and sensory in patients between two types of CTN injury (stretching or sacrificing).
- To compare the postoperative quality of life in patients between two types of CTN injury (stretching or sacrificing).
- To compare the postoperative enjoyment of food in patients between two types of CTN injury (stretching or sacrificing).
- To compare the postoperative food preference in patients between two types of CTN injury (stretching or sacrificing).
- To compare the postoperative odour identification score in patients between two types of CTN injury (stretching or sacrificing)

Other parameters:

- Age
- Gender
- Medical history
- Details of the stapes surgery or cochlear implantation

# 3. STUDY DESIGN

This study concerns a prospective study including patients who will undergo primary stapes surgery or primary cochlear implantation. The study will be performed at the department of Otorhinolaryngology in the UMCU.

The objective of this study is to evaluate the effect of CTN injury on postoperative taste function. CTN injury is a categorical variable with three categories: no touch, mobilisation and completely sectioned.

The study design is illustrated in Figure 1. Patients participate after Informed Consent (IC) is obtained. It will run for approximately two years in the UMCU. Evaluation will take place preoperatively and at 1 week, 6 weeks and 6 months postoperatively by means of taste strip test (TST), electrogustometer (EGM), Macronutrient and Taste Preference Ranking Task (MTPRT) and questionnaires (AHSP questionnaire, Health related quality of life questionnaire and a supplementary questionnaire on taste perception). Preoperatively and 1 week postoperatively the patient’s olfactory function will be evaluated using the Sniffin’ Sticks test. Three months after surgery the taste sensation is evaluated at home using questionnaires. The questionnaires will be sent by Castor or on paper. The contents of these evaluations will be explained in detail in the ‘Investigational products’ and ‘Methods’ section of this protocol.

[figure not shown]

**Figure 1.** Flowchart study procedures. TST: taste strip test, EGM: electrogustometer, AHSP: appetite, hunger and sensory perception, MTPRT: macronutrient and taste preference ranking task The symbol
[figure not shown]
 means that three months after surgery the taste sensation will be evaluated at home using three questionnaires.

# 4. STUDY POPULATION

## 4.1 Population base

The study population consists of 154 adult patients who will undergo primary stapes surgery or primary cochlear implantation.

## 4.2 Inclusion criteria

In order to be eligible to participate in this study, a subject must meet all of the following criteria:

- Signed IC form
- Age ≥ 18 years
- Patients who are planned to undergo primary stapes surgery or primary cochlear implantation
- Willingness and ability to participate in all scheduled procedures outlined in the research protocol
- Good understanding of the Dutch language

## 4.3 Exclusion criteria

A potential subject who meets any of the following criteria will be excluded from participation in this study:

- Previous middle ear surgery (with the exception of the placement of ventilation tubes in childhood)
- History of chemotherapy and/or radiotherapy
- History of facial nerve palsy
- Cardiac pacemaker
- Disability that could interfere with taste evaluation and/or questionnaire fulfilment
- Pregnancy
- History of orofacial pain
- History of dysesthesia in the orofacial region
- Local evidence of a pathological condition of the oral mucosa

## 4.4 Sample size calculation

We will perform linear regression analysis for our primary outcome measure. Including our potentially confounding covariates, a total of 12 variables will be included in the model. The variables will be injury of the chorda tympani nerve, age, gender, smoking, weight, gastroesophageal reflux, olfactory dysfunction, salivary hypofunction, medication, rhinosinusitis/allergic rhinitis, previous COVID-19 and diabetes mellitus (12–22). We have calculated that these variables are 14 degrees of freedom in total. We will include 10 patients per degree of freedom in our linear regression model. To anticipate withdrawal of 10% of participants, we will include an extra 14 patients which means we will need a sample size of 154 patients.

At the ENT department at the UMCU, 80 otosclerosis patients undergo primary stapes surgery per year and 100 patients undergo cochlear implantation per year. Assuming a participation rate of 70%, we expect to able to include 154 patients in 15 months’ time.

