## 6.5 Replacement of individual subjects after withdrawal

Subjects who withdraw from the study or who terminate the recording session prematurely will be considered as lost to follow-up. To anticipate a withdrawal of 10% of patients, fourteen more patients than needed will be recruited. Therefore, there will be no reason to replace individual subjects after withdrawal, unless more than 10% of participants will withdraw.

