# 8. STATISTICAL ANALYSIS

## All statistical analyses will be performed using the IBM SPSS Statistics version 21.0 software package (Chicago, Illinois, USA). A test for normality and histograms will be used to assess whether variables are normally distributed. We expect limited missing data. Potentially missing variables will be handled with multiple imputation.

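### The 14 extra patients in section 4.4 cover 9.1% withdrawal, not the stated 10%, and the replacement trigger in section 6.5 misses one count (minor correction)

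*Protocol*

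**What the plan says.** Section 4.4 of the protocol bases the sample size on a ratio of patients to model terms. It counts the terms ("We have calculated that these variables are 14 degrees of freedom in total") and sets the ratio ("We will include 10 patients per degree of freedom in our linear regression model"). It then adds the withdrawal allowance ("To anticipate withdrawal of 10% of participants, we will include an extra 14 patients") and reaches the total ("which means we will need a sample size of 154 patients"). Section 4.1 gives the same number for the enrolled population: "The study population consists of 154 adult patients".

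Section 6.5 restates the allowance: "To anticipate a withdrawal of 10% of patients, fourteen more patients than needed will be recruited". From this it derives an operating rule: "there will be no reason to replace individual subjects after withdrawal, unless more than 10% of participants will withdraw". The same section counts patients who withdraw as lost to follow-up.

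Section 8 adds, for missing data in general: "Potentially missing variables will be handled with multiple imputation".

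**The concern.** Sections 4.4 and 6.5 treat two things as the same: a reserve of 14 patients, and a 10% withdrawal rate among those who take part. They coincide only if the 10% is taken of the 140 needed. Withdrawals occur among the patients enrolled, and the text attaches the percentage to participants. On that base the reserve runs out before withdrawal reaches 10%.

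Two statements are affected. The first is the claim in section 4.4 that 154 allows for 10% withdrawal. The second is the rule in section 6.5, which uses 10% as the point where the reserve is exhausted and replacement becomes necessary. If the reserve is exhausted earlier, some number of withdrawals may leave the study below its own criterion while the rule says that nothing need be done.

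The ratio of patients to degrees of freedom is the only justification that section 4.4 gives for the size; it states no power, effect size or standard deviation. The criterion should therefore hold at the one withdrawal rate that the plan assumes.

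**Working it through.** **Inputs**
- Degrees of freedom: 14 (section 4.4).
- Patients per degree of freedom: 10 (section 4.4).
- Withdrawal: 10% of participants (sections 4.4 and 6.5).
- Extra patients: 14 (sections 4.4 and 6.5).
- Total enrolled: 154 (sections 4.1 and 4.4).
- Replacement trigger: more than 10% of participants withdrawn (section 6.5).

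**Number needed.** 14 × 10 = 140. The protocol does not print this figure, but 154 − 14 = 140 confirms it.

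**Reproducing the plan's total.** 140 × (1 + 0.10) = 154. This matches exactly, so the allowance was formed as 10% of the number needed.

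**What 154 delivers at the stated rate.**
- 10% of 154 = 15.4 withdrawals.
- 154 × 0.90 = 138.6 remaining, which is 1.4 below 140.
- Rate that 14 extra patients cover: 14/154 = 9.1%.

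**Total that would cover 10% of participants.** 140/(1 − 0.10) = 155.6, rounded up to 156. Check: 156 × 0.90 = 140.4, at or above 140. The difference from the plan is 2 patients.

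**The section 6.5 rule, count by count, with 154 enrolled.**
- 14 withdrawals: 14/154 = 9.1%; 140 remain; 140/14 = 10.00 per degree of freedom. No shortfall and no replacement needed.
- 15 withdrawals: 15/154 = 9.7%; 139 remain; 139/14 = 9.93 per degree of freedom. One patient short, and replacement is not triggered.
- 16 withdrawals: 16/154 = 10.4%; 138 remain; 138/14 = 9.86 per degree of freedom. Two short, but the trigger is met and replacement is open.

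The reserve is used up at 14 withdrawals and replacement opens at 16, so exactly one count, 15, falls between them. If each patient withdraws independently with probability 0.10 (an assumption made for this check), the probability of exactly 15 withdrawals among 154 is 0.107.

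**The case against.** **The denominator may be innocent.** The 10% could be meant as a share of the 140 needed, in which case 14 is exactly right. The phrase in section 6.5 about recruiting fourteen more than needed leans that way. This reading stands only in part. Section 4.4 speaks of withdrawal among participants, and section 6.5 uses a percentage of participants as its working trigger. If the 140 was the intended base, the text still has to say so, and the same wording change settles it.

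**The size rests on a rule of thumb.** A ratio of 9.93 instead of 10 alters no estimate, test or conclusion in any way that matters, and 2 patients in 156 is 1.3%. This stands, and it is why the point is only a minor correction.

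**Multiple imputation might keep some patients in the model.** Possibly, but section 6.5 counts those who withdraw as lost to follow-up, and section 4.4 itself sizes for their loss. Imputation does not clearly remove the point.

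**Stronger readings that the protocol does not support.** A reader might infer that section 6.5 leaves the shortfall unrepaired in general. It does not: from 16 withdrawals onward replacement is open, so the unrepaired shortfall is one patient at one count. A reader might also take the chance of 15 or more withdrawals among 154 as the measure of the error. That chance includes all the counts at which section 6.5 opens replacement. It also reflects mostly ordinary variation around the target: with 156 enrolled and the same independent 10% rate, the chance of 17 or more withdrawals, which would leave fewer than 140 before any replacement, is still 0.39. Neither reading should be carried forward.

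**Conclusion.** The point holds as a minor arithmetic correction. As written, section 4.4 credits 154 patients with covering 10% withdrawal among participants; they cover 9.1%. At 10%, about 138.6 remain against 140 needed, and 156 would be required. Section 6.5 carries the same equivalence into its replacement rule, with one consequence: at exactly 15 withdrawals the study stands at 139 and the rule calls for no replacement.

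The conclusion assumes that participants means the 154 enrolled, that 140 is the number needed (implied by the plan's figures, not printed), and that patients who withdraw do not count towards it. The adequacy of the 10-per-degree-of-freedom rule and the choice of model terms were not examined here. The protocol gives no power calculation, so the gap cannot be expressed as a loss of power, and nothing suggests that it threatens the study's findings.

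**What to change.** In sections 4.4 and 6.5, do one of the following:
- Keep 154 and state that it allows for 14 withdrawals, which is 9.1% of those enrolled.
- Keep the 10% rate and correct the total to 156 in sections 4.1 and 4.4, with 16 extra patients in sections 4.4 and 6.5 (156 − 140 = 16).

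In section 6.5, replace the percentage trigger with one tied to the criterion: replacement opens when fewer than 140 patients remain. With 154 enrolled this means more than 14 withdrawals; with 156 enrolled, more than 16. It would also help to print the 140 in section 4.4, so that the base of the allowance is visible.

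The first option costs only wording. The second costs two patients. On the figures in section 4.4, 70% of 80 + 100 = 180 patients a year is 126 a year, or 10.5 a month. So 156/10.5 = 14.9 months, against 154/10.5 = 14.7 months, and both fit the planned 15 months.

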# 5. NON-INVESTIGATIONAL PRODUCT 5.1 Taste Strip Test

We will also use the TST to investigate the taste ability. This objective taste test is validated in a population of healthy individuals by Mueller et al. The test will be performed according to their technique (30). The researcher will use filter paper strips, which are impregnated with four concentrations of sweet (0.4, 0.2, 0.1, and 0.05 g/mL sucrose), sour (0.3, 0.165, 0.09, and 0.05 g/mL citric acid), salty (0.25, 0.1, 0.04, and 0.016 g/mL sodium chloride), bitter (0,006, 0.0024, 0.0009, and 0.0004 g/mL quinine hydrochloride) and umami (0.03, 0.06, 0.12 and 0.25 g/mL sodium L glutamate monohydrate) tastes. Two blanked taste strips will also be used. We will present the strips in increasing concentrations in a randomized order to each side of the anterior tongue. The patient has to identify which one of the five flavours the strip is. The patient has to keep the tongue out of the mouth with the taste strip on the tongue, until he/she has made his decision by pointing to one of the five descriptors (sweet, sour, salty, bitter or umami) of the list. We will use 42 taste strips, because we want to test the taste ability of both sides of the tongue (30). Between the assessments of the taste strip the mouth will be rinsed with water. With this information we can compare the gustatory function of the area of the tongue that is innervated by the potentially injured CTN with the gustatory function of the contralateral area of the tongue. The patient will undergo this test preoperatively, 1 week, 6 weeks and 6 months postoperatively. Patients will be asked not to eat, drink (except for water), smoke or brush their teeth one hour before beginning the taste test (30). The taste strips will be ordered from Burghart Messtechnik (Germany).

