# 5.4 Electrogustometer

We will use the CE marked EGM to investigate the taste ability. Different studies have established that the EGM is a good clinical tool for measuring taste detection thresholds (23–25). Electric taste, tastes like metal and sour, will be assessed with the Electrogustometer SI-03 (Sensonics Inc., Haddon Heights, NJ). We will detect the electric taste threshold with anodal stimulation. We will stimulate from 0.25 to 450 uA using the forced-choice single staircase test procedure. The EGM manual describes the two-down one-up forced-choice single staircase procedure (see appendix 1). This taste threshold setting procedure has a correct response level of 70.7% (26,27). The stimulus duration will be set at 0.5 sec. The lowest number of uA that generates an electric taste will be determined to be the value of the taste threshold of the CTN. We will measure the taste detection threshold on the anterior and lateral region of both sides of the tongue, so we can compare the taste thresholds of the ipsilateral side of the tongue to the operated ear with the contralateral side of the tongue (see figure 1). The patient will undergo this test preoperatively, 1 week, 6 weeks and 6 months postoperatively.

[figure not shown]

Figure 2. Anterior tongue regions: anterior tongue (regions 5 and 6), lateral tongue (regions 2,3,4,7,8 and 9), central tongue (regions 11,12,13,14,15 and 16) and posterior tongue (regions 1 and 10) (28).

Different studies have established that EGM is a good clinical tool for measuring taste detection thresholds (23–25). The EGM can also assess regional taste thresholds. Sensitivity of detection is lower on the ipsilateral side of the tongue to CTN transection compared to the contralateral side of the tongue. We will measure the taste threshold of the lateral sides of the tongue (see figure 2). (29). Stimulus duration affects the threshold values and therefore the stimulus duration will be set at 0.5 sec. for all participants (28).

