# 6. METHODS

## 6.1 Study parameters/endpoints

### 6.1.1 Main study parameter

The main study parameter will be the 6 weeks postoperative amount of identified taste strips of the ipsilateral tongue of the operated ear. The range for possible scores is 0 to 20

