## 8.1 Primary study parameter

The primary study parameter is the change in the amount of identified taste strips by patient, preoperatively and 6-8 weeks postoperatively. This outcome will be presented continuous with a range from 1 to 20 identified taste strips. Mean (or the median) and standard deviation (or the range) will be reported. The effect of CTN injury on the amount of identified taste strips will be evaluated using linear regression analysis. The following confounding variables will be included in the analysis: age, gender, smoking, weight, gastroesophageal reflux, olfactory dysfunction, salivary hypofunction, medication, rhinosinusitis/allergic rhinitis, previous COVID-19 and diabetes mellitus (12–22).

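### Both tongue sides are taste-tested before surgery, but the primary regression adjusts for neither side's preoperative score

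*Protocol*

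**What the plan says.** **Data collected.** Protocol section 5.1 uses 42 strips per session to cover both sides of the tongue. The stated purpose is: "With this information we can compare the gustatory function of the area of the tongue that is innervated by the potentially injured CTN", set against the other side ("with the gustatory function of the contralateral area of the tongue"). The schedule is: "The patient will undergo this test preoperatively, 1 week, 6 weeks and 6 months postoperatively". Section 5.4 gives the same reason for measuring EGM on both sides: "so we can compare the taste thresholds of the ipsilateral side of the tongue to the operated ear with the contralateral side".

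**Endpoints.** Section 6.1.1 states: "The main study parameter will be the 6 weeks postoperative amount of identified taste strips of the ipsilateral tongue of the operated ear", with a range of 0 to 20. The five per-taste parameters in 6.1.2 are before-after differences on the ipsilateral side. The EGM parameter in 6.1.2 refers to various tongue locations and is not restricted to one side.

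**Model.** Section 8.1 states: "The effect of CTN injury on the amount of identified taste strips will be evaluated using linear regression analysis". The same section defines the primary parameter as the change from before surgery to 6-8 weeks after it, and names no side. Sections 4.4 and 8.1 list the same regressors: CTN injury and eleven patient-level factors such as age, smoking, medication and diabetes. Section 4.4 counts these as 12 variables and 14 degrees of freedom, and sets the sample size from that count. Section 6.2 says that there is no randomisation and that patient and assessor are blinded to the injury.

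**The concern.** The injury groups are not formed by randomisation, so the comparison depends on adjustment. The patient's own taste score before surgery is an obvious candidate for that adjustment. It is measured on the scale of the outcome, surgery cannot have changed it, and the trial already collects it on both sides. The plan has a closed list of regressors and it is not among them.

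Under 6.1.1 the outcome is the 6-week score, and following the plan literally would compare injury groups with no account of how well each patient tasted beforehand. Under 8.1 the outcome is a change, which uses the ipsilateral baseline, but by plain subtraction and without adjustment. Under either wording, the contralateral strips have no stated use in any taste-strip endpoint or in the primary model.

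At stake are precision of the injury contrast and control of chance or systematic baseline differences between injury groups.

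**Working it through.** **1. The plan's own figure.** 14 degrees of freedom × 10 patients = 140; 140 + 14 for withdrawal = 154. This matches section 4.4. No SD, effect size or correlation enters it, so everything below rests on assumed correlations, shown as ranges.

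**2. Where each score is used (taste strips).**

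| Score | Collected (5.1) | Endpoint (6.1.1, 6.1.2) | Primary model (4.4, 8.1) |
|---|---|---|---|
| Ipsilateral, 6 weeks | yes | yes | outcome, or part of it |
| Ipsilateral, preoperative | yes | in the per-taste differences | only inside the change, if 8.1 applies |
| Contralateral, preoperative | yes | no | no |
| Contralateral, 6 weeks | yes | no | no |

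**3. Gain from the ipsilateral baseline.** Take equal variances, scaled to 1, and a before-after correlation r. Residual variance is 1 for the 6-week score alone, 2(1 − r) for the change, and 1 − r² with the baseline as covariate.

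| r (assumed) | 6-week score alone | change | baseline as covariate |
|---|---|---|---|
| 0.6 | 1 | 0.80 | 0.64 |
| 0.7 | 1 | 0.60 | 0.51 |
| 0.8 | 1 | 0.40 | 0.36 |

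Against the 6-week score alone, residual variance falls by 36% to 64%. Against the change it falls by 20% (0.64/0.80 = 0.80) to 10% (0.36/0.40 = 0.90).

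**4. Further gain from the preoperative contralateral score.** Let a be the ipsilateral before-after correlation, b the correlation between sides at one session, and c the correlation between sides across sessions. With both preoperative scores as covariates, residual variance is 1 − (a² + c² − 2abc)/(1 − b²).

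Using assumed variance components that sum to 16 (SD 4), with side-specific variance independent between sessions:
- Patient 8, shared visit 1, side-specific 7: a = c = 8/16 = 0.5 and b = 9/16 = 0.5625. Residual variance goes from 0.75 to 0.68; 0.75/0.68 = 1.10, worth about 10% more patients.
- Patient 4, shared visit 4, side-specific 8: a = c = 4/16 = 0.25 and b = 8/16 = 0.5. It goes from 0.9375 to 0.9167; the ratio is 1.02, worth about 2% more patients.

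As a cross-check over wider correlation sets, the last column also adds the 6-week contralateral score:

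| a | b | c | ipsilateral baseline | + preoperative contralateral | + 6-week contralateral as well |
|---|---|---|---|---|---|
| 0.6 | 0.5 | 0.5 | 0.640 | 0.587 | 0.567 |
| 0.6 | 0.6 | 0.5 | 0.640 | 0.609 | 0.519 |
| 0.7 | 0.6 | 0.5 | 0.510 | 0.500 | 0.420 |
| 0.7 | 0.7 | 0.6 | 0.510 | 0.486 | 0.387 |
| 0.7 | 0.7 | 0.5 | 0.510 | 0.510 | 0.279 |
| 0.8 | 0.7 | 0.65 | 0.360 | 0.344 | 0.303 |
| 0.6 | 0.3 | 0.3 | 0.640 | 0.624 | 0.620 |

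Here the preoperative contralateral score removes between almost nothing (0.510 to 0.510) and 8% (0.587/0.640 = 0.92) of the remaining variance. In most sets the larger step comes from the 6-week contralateral score.

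**5. Cost in degrees of freedom.** One added term: 140/15 = 9.3 patients per degree of freedom. Two: 140/16 = 8.75. Holding the protocol's rule of 10 would need 150 + 15 = 165 or 160 + 16 = 176 patients.

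**The case against.** The strongest reply is that the protocol says only that the two sides can be compared. An ipsilateral outcome suits an ipsilateral nerve injury, and extra covariates are normally left to a statistical analysis plan. The first two parts are fair: an ipsilateral primary outcome is sound and is not criticised here. The third does not carry over, because section 4.4 closes the list of regressors and derives the sample size from it. A baseline score is therefore outside the model that the protocol fixes.

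A reader might go further in four ways that the document does not support.

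- **That no endpoint uses the contralateral side.** The EGM parameter in 6.1.2 is not limited to one side and 5.4 measures both, so it can include contralateral sites. The gap concerns the taste strips and the primary model.
- **That illness, practice or other visit-to-visit influences confound the result.** They do so only if they differ by injury group. Nothing in the protocol suggests this, and 6.2 blinds patient and assessor. The supplementary questionnaire on factors affecting taste is also repeated at each session (6.3). Otherwise such influences are noise.
- **That the contralateral side is worth a large gain.** A comparison with a model holding no taste baseline can be made to show the equivalent of 20 to 78% more patients under assumed inputs. That figure includes the gain from the ipsilateral baseline and should not be credited to the other side.
- **That the 6-week contralateral score belongs in the main model.** It is measured after the exposure. If that side compensates after injury, adjusting for it absorbs part of the effect.

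**Conclusion.** The point holds in a limited form. The primary model fixed in 4.4 and 8.1 omits the preoperative taste-strip scores, although both sides are measured before surgery and 5.1 announces a comparison of sides. This is a cheap improvement forgone; it does not invalidate the design.

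Most of the benefit that is safe to take comes from the ipsilateral baseline. The preoperative contralateral score adds roughly 2 to 10% in equivalent patients under the assumed variance components, and less under some other correlation sets. All these sizes assume equal variances and correlations that the protocol does not give, and they ignore whatever variance the eleven listed covariates already explain, which would shrink them.

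The size also depends on an unresolved contradiction: 6.1.1 names the 6-week ipsilateral score, while 8.1 names a change with no side and a 6-8 week window. Once the ipsilateral baseline is a covariate, the estimated injury contrast is the same for either outcome at a given time point, because subtracting a regressor from the outcome alters only that regressor's coefficient. The side and the time window would still need to be settled.

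**What to change.** 1. Reconcile 6.1.1 and 8.1: state one primary outcome (6-week ipsilateral score or change), the side, and the time window.
2. In 8.1, add the preoperative ipsilateral and preoperative contralateral taste-strip scores as covariates in the primary regression, and add them to the list in 4.4. In 8.2, do the same with the preoperative thresholds from both sides for EGM.
3. In 4.4, state that 140 evaluable patients then give about 9 per degree of freedom (9.3 with one added term, 8.75 with two) instead of 10.
4. Optionally, name a sensitivity analysis that also adjusts for the 6-week contralateral score. Report it with the contralateral change by injury group, so that readers can judge whether that side was itself affected.

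The data are already collected, so the cost is wording plus one or two degrees of freedom. If the sponsor prefers to keep 10 patients per degree of freedom, the total becomes 165 or 176. The change should be made before the injury data are unblinded, so that the choice of adjustment cannot depend on the results.
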